#### Supplemental activities

Supplemental activities will be offered several times a month and participants will be encouraged to attend. As with all study activities, participation is completely voluntary. Supplemental activities will reinforce material covered in the core intervention, encourage group physical activity, and provide additional learning opportunities. Supplemental activities will coincide with the core intervention and continue throughout the course of the study. *Promotores* will facilitate the sessions by coordinating and leading group physical activities, arranging for guest speakers on various health topics, and leading group discussions on topics raised during the core intervention. Education and activity topics will be identified by the *promotores* and research team, as well as by polling participants for topics of interest. Examples of activities include: cooking demonstrations, education on specific health topics, cultural celebrations with modified recipes, walking challenges, and Zumba® dance sessions.

#### Control

Control participants will be given the opportunity to attend educational sessions as well, although these sessions will not have the same topics as those received by the intervention participants. The control sessions will utilize RAC leadership training material for farmworkers on: empathy, communication, conflict resolution, and sharing knowledge. Sessions for control participants will also be held at the ranch during a meal break. Recruitment and follow-up for control participants will follow the same approach as those for intervention participants.

### Retention

After collection of baseline data via the Baseline questionnaire, intervention participants receive the education sessions. If a participant attends less than three sessions, they are no longer eligible to participate in the study. Research assistants will attempt to contact the participant to administer an Exit questionnaire. The purpose of the Exit questionnaire is to collect information regarding the reasons why the participant was unable or unwilling to attend the sessions. All participants (control and intervention) are administered follow-up questionnaires at 3, 6 and 12 months. The final follow-up will take place at 1.5 years. To aid in retaining participants, research assistant will send postcards to participants to remind them of their upcoming appointments. Research assistants will also call participants a minimum of ten times. Once a participant (intervention and control) is in the study they will remain in the study and be followed until their enrollment period ends.

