## Methods

### Study design

A cluster randomized trial (CRT) design is being used to evaluate the effectiveness of a worksite lifestyle intervention in producing changes in factors known to increase risk of obesity and diabetes [23]. Ranches allocated to the intervention group will receive the worksite intervention program over 6–12 weeks. Ranches allocated to the control group will receive no intervention but will be given the opportunity to attend other educational sessions, topics covered will not be the same as those covered in the intervention program and may include such topics as communication and conflict resolution specifically geared towards farm workers. The study period is 5 years. Recruitment and enrollment of subjects is expected to take 2 years. Recruitment at ranches will be staggered so that as work crews have a sufficient number of interested participants and baseline assessments are completed, the educational sessions will begin on designated ranches. A subject’s participation in the study will begin with their consent and end after a 1.5-year follow-up data collection point, or at an earlier date if they choose to withdraw from the study (Fig. 1).

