#### Intervention

UCD, in collaboration with RAC, developed a program by integrating aspects of several programs to create a culturally tailored curriculum appropriate for delivery in an agricultural setting. The program was designed to educate participants about obesity, diabetes and healthy lifestyles, motivate changes in their current diet habits, and provide a supportive participatory group setting. Core principles of *Salud para su Corazon*, developed by the U.S. National Heart, Blood and Lung Institute (NHLBI) are complemented with *5 Pasos*, being implemented in Mexico by the Mexican Government [24, 25]. These two programs are used synergistically to implement the goals of the intervention. Because of the simplicity of its message, *5 Pasos* provides the general framework for the program. The five steps are: 1) Move, 2) Drink water, 3) Eat fruits and vegetables, 4) Measure (food portions and weight), and 5) Share (information learned and healthy habits). The *Salud para su Corazon* curriculum is a user-friendly, bilingual program for *promotores* developed by NHLBI specifically for Latino communities. The *Salud* curriculum will be used to supplement some of the visual aids used during the delivery of the intervention program. The intervention will be implemented on farms where workers spend a considerable amount of time every day. The intervention will be delivered over 6–12 weeks and the length of follow-up will be 1 or 1.5 years depending on when the worker was enrolled in the study.

The core intervention program will consist of 12 lessons (Table 1). In order to maximize participation and retention in this group which averages long work hours, the core intervention sessions will take place at the ranch during a meal break during work hours. Sessions will be presented to work crews in a format analogous to tailgate trainings. Tailgate trainings are gatherings of small groups of workers around the tailgate of a truck, in the field, or other spot for a brief, informal and focused training session on a single topic.

**Table 1 Tab1:** PASOS Curriculum

Session	Topic
1	Introduction to PASOS and the five steps toward a healthy lifestyle
2	Understanding the importance of having a healthy heart
3	Body mass index
4	Understanding blood pressure and keeping it within healthy levels
5	Learning about diabetes
6	Understanding diabetes and side effects
7	Understanding cholesterol and keeping it within healthy levels
8	Children and overweight

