### Statistical analysis plan

Analyses will use a modified intent-to-treat basis to assess the effects of the intervention regardless of adherence [37, 38]. Data collected for the primary outcome will be analyzed and summarized by standard descriptive statistics. We will analyze continuous outcomes (body weight and BMI change from baseline to end of follow-up and between intervention and control) using the mixed effects model accounting for ranch as a cluster variable. Control of other important covariates such as gender, baseline weight/BMI may be made in sensitivity analyses. Analysis of secondary outcomes will be conducted in a similar fashion. In these analyses, we will estimate ICC and report them along with other design characteristics including cluster size and number of clusters. We will not adjust for multiple testing in the analysis of the primary outcome (weight and BMI, which are virtually a single outcome as height does not change), but clearly report the analyses of secondary outcomes as secondary in publication. No interim analyses will be conducted.

Data collected to address economic evaluation, including intervention costs, health outcomes and medical costs, and worker productivity will be combined with accounting data to assess the overall economic cost/gain of the intervention. Accounting data will be compared to costs produced by the UCD Department of Agricultural and Resource Economics, which does not include costs of obesity program interventions, but does provide guidance on related issues. For example, a ranch benefits economically if a worker’s harvesting rate improves because overall harvest cost falls when worker productivity improves. Moreover, absenteeism adds uncertainty and cost of maintaining a larger workforce for equivalent production.

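### The rule that removes participants with fewer than three sessions is a post-randomisation exclusion on adherence, and it conflicts with the analysis and follow-up that the protocol promises

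*Protocol article*

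**What the plan says.** All of this is in the protocol article.

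- **Retention**, opening: "After collection of baseline data via the Baseline questionnaire, intervention participants receive the education sessions". The next sentence is the rule: "If a participant attends less than three sessions, they are no longer eligible to participate in the study". After it: "Research assistants will attempt to contact the participant to administer an Exit questionnaire". The stated purpose of that questionnaire is to learn why the worker did not attend. No weight measurement is mentioned for these workers.
- **Retention**, last sentence: "Once a participant (intervention and control) is in the study they will remain in the study and be followed until their enrollment period ends".
- **Statistical analysis plan**: "Analyses will use a modified intent-to-treat basis to assess the effects of the intervention regardless of adherence". The article does not say what is modified.
- **Study design** and **Control**: control ranches "will be given the opportunity to attend other educational sessions", and "Control participants will be given the opportunity to attend educational sessions as well". No minimum attendance is stated for them.
- **Intervention**: "The core intervention program will consist of 12 lessons", so the threshold is three of twelve.

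**The concern.** Ranches are randomised before workers are recruited, and the rule operates after consent and baseline data collection. A worker's place in the study therefore depends on what they do after allocation, and what they do is attend or not attend the program under test.

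Workers who drop out of the sessions early are plausibly less motivated and would plausibly lose less weight. If they leave the intervention arm while comparable workers stay in the control arm, the comparison is likely to favour the program even if it does nothing. A larger sample does not reduce such a bias. If follow-up weights are not taken for these workers, any correction at analysis rests on missing-data assumptions that the data cannot test. Percent change in weight is a primary outcome, so the main result is affected.

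**Working it through.** **1. The plan's own figures.** No figure in the article depends on this rule. For scale, the Power calculation section plans on differences of 4% and 3%, SD 5%, two-sided alpha 5% and 80% power. A two-sample t-test gives 25.5 and 44.6 per group, rounded up to 26 and 45, so totals of 52 and 90. These match the article.

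**2. The passages applied to one worker.** Take an intervention worker with a baseline weight who attends two sessions.

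- Under the rule, this worker is out of the study and is sought only for the Exit questionnaire.
- Under the last sentence of Retention, this worker stays in and is followed.
- Under the analysis section, this worker's attendance should not matter.

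The first instruction cannot be reconciled with the third. It also conflicts with the second, unless being in the study is taken to mean having passed the threshold.

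**3. Which arm.** The rule speaks of a participant without naming an arm. It directly follows the sentence on intervention sessions, and control sessions are only offered. The intervention arm alone is the natural reading, but it is an inference.

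**4. Size, as illustration only.** The article gives neither the share attending fewer than three sessions nor how their weight change would differ. Both are assumed here, with no true effect and all controls kept.

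*Model A.* Attendance propensity and percent weight loss are jointly normal with correlation r, and the lowest fraction q of attenders is removed. With c the q-quantile of the standard normal,

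shift = r × SD × φ(c)/(1 − q), with SD = 5%.

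| q | φ(c)/(1 − q) | r = 0.2 | r = 0.3 |
|---|---|---|---|
| 20% | 0.280/0.80 = 0.350 | 0.35 | 0.52 |
| 30% | 0.348/0.70 = 0.497 | 0.50 | 0.75 |

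The shift is 0.35 to 0.75 percentage points, which is 0.35/3 = 12% to 0.75/3 = 25% of the 3% planning difference.

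*Model B.* Those removed would have lost g points less than those kept, so shift = q × g. With q from 10% to 30% and g from 1 to 3 points, this runs from 0.10 × 1 = 0.1 to 0.30 × 3 = 0.9 points. The gap implied by model A is shift/q, from 0.50/0.3 = 1.7 to 0.52/0.2 = 2.6 points, which lies inside that range.

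*Effect on type I error under model B.* Take 300 per arm (600 workers, 1:1) and the article's inflation formula with clusters of 100:

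SE = 5 × √{[1 + 99 × ICC] × [1/(300(1 − q)) + 1/300]}

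For q = 30%, g = 3 and ICC 0.01, SE = 5 × √{1.99 × (1/210 + 1/300)} = 0.635. The shift is then 0.9/0.635 = 1.42 standard errors, and a nominal 5% test rejects 29% of the time. Over the whole grid the rate is 5.3% to 29% at ICC 0.01 and 5.1% to 13% at ICC 0.05. This is a normal approximation that ignores the small number of ranches, so it is rough. The factor 1.99 comes from the stated formula; the inflation factors printed in Table 2 are larger, which is a separate matter.

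**5. What keeping everyone costs in power.** If the 10% to 30% of low attenders gain nothing from the program (also assumed), a 3% difference becomes 3 × (1 − q) = 2.7% to 2.1%. The individually randomised total then rises from 90 to between 110 and 180. A 4% difference becomes 3.6% to 2.8%, and the total rises from 52 to between 64 and 104.

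**The case against.** The strongest reply is that the analysis is *modified* intent-to-treat. The term could mean a minimum-exposure population of at least three of twelve sessions, analysed without regard to adherence beyond that, with the definition in a fuller document not shown here. That may be the intention. It does not remove the conflict, because a population chosen by attendance is not analysed irrespective of adherence, whatever the label. Likewise, the last sentence of Retention can be read as covering only those past the threshold. This would weaken the contradiction within that section, but not the exclusion itself.

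Several stronger statements are tempting and are not supported.

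- *That the rule certainly applies to one arm and certainly favours the program.* The Control section says that control recruitment and follow-up take the same approach, and the inclusion criteria require every worker to be willing to attend weekly sessions. If the rule covers both arms, the direction of bias is no longer clear. It would still be an adherence exclusion, since three health sessions and three leadership sessions select different workers.
- *That non-attenders' follow-up weights are never collected, so the promised analysis is impossible.* The article contradicts itself on follow-up, so it does not settle what is done.
- *That the damage cannot be repaired.* Baseline weight, covariates and attendance records allow weighting, imputation or bounds. These help only in part, and only under untestable assumptions.
- *That the pilot's 70% retention supports removing 30%.* That figure is overall retention to post-intervention, not split by arm or attendance.

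Some low attenders would also be lost through ordinary attrition, so not all of the calculated shift would be due to this rule.

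**Conclusion.** The point stands as a defect in what the article states. The rule excludes participants after randomisation on adherence. It conflicts with the analysis section under any meaning of *modified* and, on its natural reading, with the last sentence of Retention. Bias towards the program is likely if the rule operates in one arm, but it is not proven.

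Its size cannot be derived from the article. The 0.35 to 0.75 percentage points rest on SD 5%, which the article uses, and on an assumed correlation of 0.2 to 0.3 and an assumed 20% to 30% removed, which it does not give. Confidence is high on the conflict and lower on the direction and size.

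**What to change.** Reconcile the Retention and Statistical analysis plan sections by treating stopping sessions and stopping outcome measurement as two different things.

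1. Keep every consented, eligible worker with a baseline weight in outcome follow-up at all visits, whatever their attendance, and analyse them in the arm to which their ranch was randomised.
2. Use attendance of at least three sessions only to define a labelled secondary per-protocol or complier analysis.
3. State what *modified* means, without reference to attendance.
4. For workers already removed, attempt weights at the remaining visits where consent and ethics approval allow. The article reports follow-up as ongoing, so some visits may still be open; those already missed cannot be recovered.
5. Report the number removed under the rule by arm, with a sensitivity analysis for their missing outcomes.

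The cost is an amendment reviewed by the institutional review board, the effort of recontacting workers who were told they were no longer in the study, and extra visits and gift cards. The estimated effect will probably be smaller, with some loss of power, as step 5 of the working illustrates.

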### Incentives

Subjects will be given a $25 gift card at the baseline, post-intervention, and 6-month data collection points and a $50 gift card at the 1 and 1.5-year data collection point. Participants may be given a water bottle and/or bandana (or other similarly valued items) at the end of the educational sessions or at supplemental activities. All control participants in matched ranches will complete follow-up data collection at approximately the same time as their intervention work crew.

### Power calculation and sample size

For a CRT, we computed sample size (N) assuming independence (i.e., simple random sampling) suited for standard randomized control trial (RCT) that randomizes individuals to interventions, and then multiplied the resulting sample size estimate by the inflation factor (IF). Here, IF is defined as IF = [1 + (m-1)*ρ], where m is the average cluster size and ρ is the intra-class correlation (ICC). For the N calculation under simple random sampling, we used the estimates reported from Ackerman et al. [26]. In this study, the intervention group achieved 6% weight loss and control group achieved 2% weight loss, at 4–6 and 12–14 months of follow-up with standard deviation (SD) approximately 4.4% in both groups, where percent weight loss was the primary outcome [26]. In our calculations, we used somewhat conservative estimates: mean difference of 4 and 3% with SD of 5%. To achieve 80% power with alpha level of 5% using two-sided, two-sample t-test, the minimal total N required for detecting 4% difference is 52 (26 per group) and that for detecting 3% difference is 90 (45 per group). Noting that the average cluster (ranch) size in our study is 100, Table 2 provides estimates of total N and the number of clusters needed for different values of ICC and mean difference in the outcome. Based on these calculations, we believe a total of 4–6 clusters may be justifiable. However, we understand the possibility of confounding between intervention effect and cluster effects (i.e. ranch in this study), and these potential limitations in generalizability will be accounted for in data analyses and acknowledged in interpreting the results.

**Table 2 Tab2:** Power/Sample size calculations

Mean difference (SD = 5%)	ICC	IF	Total N needed for individual randomization	Total N needed for CRT	Total # of clusters = N/100^a^
4%	0.01	2.99	52	156	2
	0.02	4.98	52	259	4
	0.05	10.95	52	570	6
3%	0.01	2.99	90	270	4
	0.02	4.98	90	449	6
	0.05	10.95	90	986	10

^a^Rounded up to even number integer

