### Randomization

Randomization will take place at the ranch level prior to recruitment of participants into the study. Two ranches matched on location, type of berry, size (whenever feasible) will be randomized with the 1:1 ratio sequentially when the two ranches are available for participation, using a uniform distribution for random number generation. At least six ranches will be randomized to intervention or control. We will recruit approximately 100 workers at each ranch. In total, the study will recruit up to 600 workers. Due to the nature of the intervention and because the intervention takes place at the ranch, the participants as well as the research assistants collecting data will not be blinded.

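### Table 2's inflation factors correspond to 200 workers per ranch, not the stated 100, so all six trial sample sizes and five of six ranch counts do not follow from the stated inputs

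*Protocol article*

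**What the plan says.** The protocol article, under Power calculation and sample size, starts from a two-sided two-sample t-test at 5% alpha and 80% power with an SD of 5%. This gives a total of 52 for a 4% difference and 90 for a 3% difference. These totals are then multiplied by an inflation factor: "IF is defined as IF = [1 + (m-1)*ρ], where m is the average cluster size and ρ is the intra-class correlation (ICC"). The value of m is given in the same section: "Noting that the average cluster (ranch) size in our study is 100, Table 2 provides estimates of total N".

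The Randomization section agrees on ranch size: "We will recruit approximately 100 workers at each ranch". It also fixes the scale of the trial: "At least six ranches will be randomized to intervention or control", and "In total, the study will recruit up to 600 workers".

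Table 2 lists the inflation factor, the total N for the cluster trial and the number of clusters for ICCs of 0.01, 0.02 and 0.05. The number of clusters is N/100 rounded up to an even integer. From these rows the section concludes that four to six ranches can be justified.

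**The concern.** The printed inflation factors (2.99, 4.98 and 10.95) are too large for clusters of 100. At an ICC of 0.01, for example, 99 further members add 0.99 to the factor, not 1.99. The column that converts N into ranches does use 100, so the table appears to contain two different cluster sizes.

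Table 2 is the only justification the article gives for the number of ranches. If its entries do not follow from the stated formula and inputs, a reader cannot tell which combinations of difference and ICC the planned six ranches of 100 were meant to cover. As printed, a 3% difference with an ICC of 0.05 needs 986 workers in 10 ranches, well beyond the plan.

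**Working it through.** **Inputs.** All are from Power calculation and sample size: difference 4% or 3%, SD 5%, alpha 5% two-sided, power 80%, m = 100, ICC 0.01/0.02/0.05, ranch count = N/100 rounded up to even.

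**Step 1: the individually randomised N.** The two-sample t-test needs 25.52, rounded up to 26 per group, for d = 4/5 = 0.8. It needs 44.59, rounded up to 45 per group, for d = 3/5 = 0.6. The totals of 52 and 90 reproduce, so the fault lies in the inflation step.

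**Step 2: the cluster size implied by Table 2.** Solve m = (IF − 1)/ICC + 1:

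- (2.99 − 1)/0.01 + 1 = 200
- (4.98 − 1)/0.02 + 1 = 200
- (10.95 − 1)/0.05 + 1 = 200

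With m = 200 all six printed N values reproduce after rounding up: 52 × 2.99 = 155.48 → 156; 52 × 4.98 = 258.96 → 259; 52 × 10.95 = 569.4 → 570; 90 × 2.99 = 269.1 → 270; 90 × 4.98 = 448.2 → 449; 90 × 10.95 = 985.5 → 986. Dividing these by 100 and rounding up to even gives all six printed ranch counts. With m = 99, 100 or 101, none of the six reproduces.

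**Step 3: the table at the stated m = 100.** IF = 1 + 99 × ICC.

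| Difference | ICC | IF printed | IF at m = 100 | N printed | N at m = 100 | Ranches printed | Ranches at m = 100 |
|---|---|---|---|---|---|---|---|
| 4% | 0.01 | 2.99 | 1.99 | 156 | 103.48 → 104 | 2 | 2 |
| 4% | 0.02 | 4.98 | 2.98 | 259 | 154.96 → 155 | 4 | 2 |
| 4% | 0.05 | 10.95 | 5.95 | 570 | 309.4 → 310 | 6 | 4 |
| 3% | 0.01 | 2.99 | 1.99 | 270 | 179.1 → 180 | 4 | 2 |
| 3% | 0.02 | 4.98 | 2.98 | 449 | 268.2 → 269 | 6 | 4 |
| 3% | 0.05 | 10.95 | 5.95 | 986 | 535.5 → 536 | 10 | 6 |

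Overstatement of the factor: 2.99/1.99 = 1.50, 4.98/2.98 = 1.67, 10.95/5.95 = 1.84.

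**Step 4: the alternative reading, m = 200 intended.** The factors and N values would then stand, but the divisor would be wrong. N/200 rounded up to even gives 2/2/4 and 2/4/6, so the same five counts change. The 3%, ICC 0.05 row would still need 986 workers, against a maximum of 600.

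**Step 5: how far the corrected counts can be trusted.** At m = 100, three rows call for two ranches in total, one per arm. That leaves 2 − 2 = 0 between-ranch degrees of freedom. For six ranches of 100, a 3% difference and ICC 0.05, the standard error is 5 × √(5.95 × 2/300) = 0.996 and the standardised difference is 3/0.996 = 3.01. The normal approximation gives 85% power; a t-test on 6 − 2 = 4 degrees of freedom gives 62%. For four ranches of 100, a 4% difference and ICC 0.05, the figures are 91% and 44% (2 degrees of freedom). These calculations assume equal ranch sizes and ignore the matching of ranches.

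**The case against.** The strongest reply is that the error is conservative and does no harm to the design. It overstates the requirement. By the document's own method at m = 100, the most demanding row needs 536 workers in six ranches, and 6 × 100 = 600 covers it. This remains so with losses at the pilot's 70% retention, which was measured only to the end of the intervention: m = 70 gives IF = 1 + 69 × 0.05 = 4.45 and N = 90 × 4.45 = 400.5 → 401, against 6 × 70 = 420 retained. The article also says that follow-up is ongoing, so a corrected table cannot change how many ranches were enrolled. The loss of power from few degrees of freedom is a separate weakness, present whichever factor is printed.

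All of that stands as to consequence, and the shortage of degrees of freedom should not be counted as part of this error. It does not rescue the table. The excess is not declared as a safety margin, and the section draws its conclusion about the number of ranches directly from these rows.

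A second reply is that 200 may have been the intended size, in which case the N values are right. This cannot be excluded from the printed numbers alone. However, the text of the section, the table's own divisor and the Randomization section all say 100, nothing in the article mentions 200, and five ranch counts change on that reading too.

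**Conclusion.** Table 2 contradicts its own formula and stated inputs. At the stated 100 workers per ranch, all six inflation factors and all six total N values are wrong, overstated by about 50%, 67% and 84% at ICCs of 0.01, 0.02 and 0.05. Five of the six ranch counts are wrong; only the row for a 4% difference with ICC 0.01 is unchanged. The arithmetic is exact and rests only on figures in the article. An error in reading the PDF is not a plausible explanation, because every printed N and ranch count follows from the printed factors.

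The error does not make the planned 600 workers in six ranches too small by the document's method. It does mean that the published justification misreports what that design covers: at m = 100 the 3%, ICC 0.05 scenario falls within the plan instead of far outside it. The power figures of 62% and 44% are illustrative and depend on the assumptions given with them.

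**What to change.** Recompute Table 2 with a single cluster size and restate the sentence that draws the number of ranches from it. With m = 100 the entries are:

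- IF 1.99/2.98/5.95
- total N 104/155/310 for a 4% difference and 180/269/536 for 3%
- ranches 2/2/4 and 2/4/6

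If 200 per ranch was intended, say so, divide by 200, and reconcile this with the 100 per ranch and the 600 total given elsewhere.

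In the same revision, base the conclusion on a power calculation that uses the between-ranch degrees of freedom. That correction works in the opposite direction, and the smaller counts would otherwise suggest that two or four ranches are enough.

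The cost is one table and one sentence, plus a short power calculation. Recruitment does not change.

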### Preliminary data from pilot study

In 2010, University of California, Davis (UCD) collaborated with Reiter Affiliated Companies (RAC), the largest fresh multi-berry producer in the world, growing Driscoll’s proprietary varieties of strawberries, raspberries, blueberries, and blackberries year round in the US, and other international locations, on a pilot study [23]. In this randomized controlled study, 254 participants were allocated to either the control or intervention group in a 1:2 ratio for control:intervention. Farmworkers employed by RAC participated in a 10-week diabetes and obesity prevention program developed by UC Davis and delivered in Spanish by *promotores*. The majority of participants were born in Mexico and identified Spanish as their native language. Primary outcomes included change in weight, body mass index (BMI), waist circumference, and fasting blood glucose concentration. Secondary outcomes assessed changes in diet and physical activity. The pilot found small but significant reductions in weight, BMI and waist circumference in participants completing the program; the decreases were statistically significant in women, but not in men. Improvement in knowledge of healthy eating such as the number of recommended servings of fruits and vegetables, how much water to drink and how much to exercise per day was also seen. Self-reported behaviors related to a healthy lifestyle also changed in the positive direction. Participants who completed the program reported increased physical activity as well as changing their eating habits, such as eating more fruit and less fast food, drinking more water and fewer sweetened drinks. Participant retention was high, with 70% overall remaining in the study from baseline to post-intervention [23]. After the successful completion of the pilot study, we aim to implement and evaluate the effectiveness of the program on a larger scale by recruiting more participants and with a longer follow-up period. The central hypotheses of this project are that a lifestyle intervention delivered at the agricultural worksite will reduce obesity and diabetes risk for employees and will prove to be cost effective for the employer.

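### Table 2 ignores the between-ranch degrees of freedom, so its two-ranch and four-ranch rows, and the lower end of the 4–6 cluster conclusion, do not deliver the stated 80% power

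*Protocol article*

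**What the plan says.** The section on power and sample size starts from individual randomization: "To achieve 80% power with alpha level of 5% using two-sided, two-sample t-test", with a "mean difference of 4 and 3% with SD of 5" per cent. This gives 52 in total for a 4% difference and 90 for 3%. The totals are then inflated: "IF is defined as IF = [1 + (m-1)*ρ], where m is the average cluster size". The section also states that "the average cluster (ranch) size in our study is 100".

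Table 2 multiplies 52 and 90 by printed inflation factors of 2.99, 4.98 and 10.95 (ICC 0.01, 0.02, 0.05), divides by 100 and rounds up to an even number. The ranch counts are 2, 4 and 6 for a 4% difference and 4, 6 and 10 for 3%. The conclusion is "Based on these calculations, we believe a total of 4–6 clusters may be justifiable".

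The Randomization section says "At least six ranches will be randomized to intervention or control", in matched pairs, with about 100 workers per ranch and up to 600 in all. The Statistical analysis plan section names a mixed model with ranch as the cluster.

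**The concern.** The design effect corrects the variance of the treatment contrast but not the reference distribution. Ranches are randomized, so the contrast is judged against variation between ranches. Without pairing, that leaves 2 degrees of freedom with four ranches, 4 with six and none with two. The two-sided 5% critical values are 4.30 on 2 df and 2.78 on 4 df. The t-test behind 52 and 90 used 50 and 88 df, with critical values near 2.0.

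A row that claims 80% power with two or four ranches is therefore not supported by its own calculation. The document also states no power for the six-ranch minimum, so a reader who meets a null result could take the trial to be powered at 80% across the table.

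**Working it through.** **Inputs.** SD 5%, differences 4% and 3%, ICC 0.01/0.02/0.05, m = 100 per ranch, two-sided alpha 0.05 (all from Power calculation and sample size). At least six ranches (Randomization). The case of 70 analysed per ranch is an assumption taken from the pilot (Preliminary data from pilot study): "Participant retention was high, with 70% overall remaining in the study from baseline to post-intervention".

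**Step 1: the plan's own figures.** The exact two-sample t-test gives 26 and 45 per group, so 52 and 90 reproduce. The products and ranch counts follow from the printed inflation factors (for example 52 × 4.98 = 258.96, so 259, so 4 ranches). The printed factors do not follow from the stated m:

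| ICC | 1 + 99 × ICC (m = 100) | 1 + 199 × ICC (m = 200) | Printed |
|---|---|---|---|
| 0.01 | 1.99 | 2.99 | 2.99 |
| 0.02 | 2.98 | 4.98 | 4.98 |
| 0.05 | 5.95 | 10.95 | 10.95 |

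**Step 2: power of the printed rows.** With g ranches per arm, SE = SD × √(2 × IF / (g × m)). Power comes from the noncentral t with noncentrality difference/SE and df = ranches − 2, using IF = 1 + 99 × ICC.

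| Row | Ranches | df | SE (%) | Noncentrality | Power |
|---|---|---|---|---|---|
| 4%, 0.01 | 2 | 0 | – | – | no test |
| 4%, 0.02 | 4 | 2 | 5√(2×2.98/200) = 0.863 | 4.63 | 66.7% |
| 4%, 0.05 | 6 | 4 | 5√(2×5.95/300) = 0.996 | 4.02 | 84.6% |
| 3%, 0.01 | 4 | 2 | 5√(2×1.99/200) = 0.705 | 4.25 | 60.7% |
| 3%, 0.02 | 6 | 4 | 5√(2×2.98/300) = 0.705 | 4.26 | 88.2% |
| 3%, 0.05 | 10 | 8 | 5√(2×5.95/500) = 0.771 | 3.89 | 92.4% |

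With normal critical values the two four-ranch rows would show 99.6% and 98.9%, so the shortfall comes from the degrees of freedom.

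**Step 3: correcting only the inflation factor.** The table's method then gives N = 104, 155 and 310 for 4% (52 × 1.99, 2.98, 5.95, rounded up) and 180, 269 and 536 for 3% (90 × the same). The counts become 2/2/4 and 2/4/6. Three rows would allow no test. The others would have 43.8% (4%, ICC 0.05, four ranches), 47.3% (3%, ICC 0.02, four) and 62.3% (3%, ICC 0.05, six). The inflated factors had been partly masking the missing degrees of freedom.

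**Step 4: six ranches, the planned minimum.** Power is listed for ICC 0.01/0.02/0.05. At m = 70 the inflation factors are 1.69/2.38/4.45.

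| Analysis | Analysed per ranch | df | 4% difference | 3% difference |
|---|---|---|---|---|
| Unpaired | 100 | 4 | 99.9/98.4/84.6% | 96.7/88.2/62.3% |
| Unpaired | 70 | 4 | 99.5/97.2/82.4% | 93.4/84.1/59.6% |
| Matched pairs, no variance gain | 100 | 2 | 91/80/57% | 75/61/39% |

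**Step 5: detectable difference, six ranches, unpaired, 80% power.** The noncentrality needed on 4 df is 3.761.
- 100 analysed: 3.761 × 0.576/0.705/0.996 = about 2.17/2.65/3.75%.
- 70 analysed: 3.761 × 0.634/0.753/1.029 = about 2.39/2.83/3.87%.

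**The case against.** The strongest reply is that the trial does not plan two or four ranches. The Randomization section commits to at least six, and under an unpaired analysis six exceed 80% in five of six scenarios, including with 70 analysed per ranch. That stands. It confines the defect to what the sample size section prints and concludes, and it means that no extra ranches are called for. A reader might infer that the trial as planned is generally underpowered; the documents do not support that.

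A reader might also apply four ranches to every scenario and report 29% to 67% power in five of the six. That is not a fair reading. For 4% at ICC 0.05 and 3% at ICC 0.02 Table 2 asks for six ranches, and for 3% at ICC 0.05 it asks for ten. At those counts power is 85%, 88% and 92%. The conclusion is also hedged: four to six may be justifiable, beside a table that openly shows ten in one row.

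Attrition is a further temptation. The calculation allows for no loss, and the 4%, ICC 0.05 row needs 570 of at most 600. But 570 rests on the printed factor of 10.95; with 5.95 the figure is 310. With six ranches, 30% loss moves the detectable difference only from 3.75% to 3.87% at ICC 0.05. Attrition belongs in the restated figures but does not cause the shortfall.

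The caveat about confounding of intervention and ranch effects follows the 4–6 conclusion, so it should not be read as a promise to rescue a two-ranch design.

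Finally, the protocol gives no degrees-of-freedom method for the mixed model, and it may properly leave that to an analysis plan not shown here. This does not rescue the four-ranch rows: using a critical value near 2 with four ranches would gain power only by giving up the stated 5% alpha.

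**Conclusion.** The point holds for three rows of Table 2 and for the lower end of the 4–6 range. The two four-ranch rows have 67% and 61% power against a stated 80%, and the two-ranch row cannot be tested because ranch and treatment coincide. The six- and ten-ranch rows exceed 80%. The printed inflation factors are a second error, in the opposite direction, and the two must be corrected together.

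For the six-ranch minimum, the one scenario not powered at 80% under an unpaired analysis is 3% at ICC 0.05: 62% with 100 analysed per ranch, 60% with 70.

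These figures assume equal ranch sizes, SD 5%, the protocol's ICC values and an analysis that does not use the pairs. If the pairs are analysed and matching brings no reduction in variance, six ranches have 2 df and only 4% at ICC 0.01 and 0.02 reach 80%. Any variance gain from matching would improve on that; the documents give no figure for it.

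**What to change.** In the sample size section and Table 2:

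- Correct the inflation factors to 1.99, 2.98 and 5.95 and, in the same revision, base power on t with (ranches − 2) df. Do not correct the factors alone.
- Delete the two-ranch row and replace the 4–6 conclusion with the minimum of six ranches in the Randomization section. A four-ranch entry is not worth keeping even for 4% at ICC 0.01: it reaches 80.2% with 100 analysed per ranch but 73.9% with 70.
- State the power of six ranches in all six scenarios with 100 and with 70 analysed per ranch (the unpaired rows of the six-ranch table above), naming the 30% loss as an assumption from the pilot.
- State the detectable differences for six ranches at 80% power: about 2.17/2.65/3.75% with 100 analysed and 2.39/2.83/3.87% with 70, at ICC 0.01/0.02/0.05. Say plainly that 3% at ICC 0.05 is not powered at 80%.
- Say whether the matched pairs enter the analysis. If they do, report the 2 df figures, or a justified variance gain from matching.

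The cost is restated figures only: no extra ranches or participants and no change to conduct. The stated power becomes less favourable.
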